### Outcomes and Data Collection Methods

Pupils who consented to participate were asked to complete a baseline assessment. This involved participating in a series of game theory experiments and completing a self-report questionnaire.

#### Game Theory Experiments

In order to identify social norms and their role in supporting smoking prevention interventions in schools, we triangulate the findings from a number of different game theory experiments, conducted before and after the smoking prevention interventions. In all of these incentivized experiments, monetary amounts were presented in cash in Northern Ireland and a gift card in Bogotá. Game Theory Experiments and questionnaires were delivered via Qualtrics (www.Qualtrics.com) and collected using tablet computers in each school.

As previously validated (18), the extent of rule-following in the RF task provides a measure of individual norm-following proclivity and this norm sensitivity measure is a good explanation for cooperation, reciprocity and prosocial behavior across decision contexts (18). In this task, an individual gets the largest payoff by breaking the rule and the smallest payoff by following the rule completely. Thus, the more a participant cares intrinsically about rule-following the more willing he/she will be to incur costs of doing so (18). The choices that participants make allow us to test whether those who reveal a stronger preference for following norms will be more likely in other contexts to be influenced by social norms (as was demonstrated in the original study) (18).

##### Measuring injunctive and descriptive norms

Injunctive norms reflect shared beliefs about what actions people *ought to* take; descriptive norms reflect shared beliefs about the prevalence of the norm (rather than beliefs about the behaviors that ought to be influenced by the norm). To measure injunctive and descriptive norms, we followed a protocol developed by Krupka and Weber (17). In a series of Coordination games, participants rated the social appropriateness of various actions that others might take and, in addition, they estimated the frequency with which people actually engage in certain behaviors. These games provide respondents with incentives to *match* their ratings/estimates to the responses of other participants in their year group in the session rather than to provide their personal opinions. In summary, we are measuring first-order beliefs about the prevalence of a norm against smoking/vaping and second-order beliefs about the social appropriateness of various smoking/vaping related behaviors.

The protocol measures injunctive norms because it creates an incentive to anticipate the extent to which others will rate an action as socially appropriate or inappropriate, and to respond accordingly. That is, if there is a social norm that some actions are more or less socially appropriate, respondents attempting to match others' appropriateness ratings are likely to rely on this shared perception to help them do so. Thus, the protocol elicits collective perceptions of appropriateness—our empirical measure of an injunctive social norm. This protocol was adapted to measure injunctive norms of prosocial behavior, injunctive norms about smoking behavior, and descriptive norms about smoking behavior. To encourage participants to *match* their ratings/estimates to the responses of other participants in their year group, they were paid £10.00 in Northern Ireland and £3.43 in Colombia for one “part” in the experiment only if their response was the same as the most common response given by other participants for a randomly selected question in that part of the experiment. For each “part” of the experiment, participants were told that at the end of the intervention, a coin would be flipped to determine whether they received their earnings from the baseline experiment or the experiment conducted after the intervention.

##### Defining and identifying social norms unrelated to smoking

We first elicited pro-sociality norms unrelated to smoking behavior (as one type of negative control). We used a vignette describing a hypothetical Dictator game scenario as per Krupka and Weber (17) and Kimbrough et al. (18). The Dictator game is commonly used as a measure of social preferences, in particular, altruism (48). Such norms are unlikely to be affected by interventions targeted at altering smoking behavior. Hence, we measured norms of altruism before and after the intervention, as a “negative control.” We do not expect altruism norms to change after the smoking prevention interventions. In our norm elicitation experiment participants read a vignette that describes the choices an “Individual A” would be faced with, within the Dictator Game. “Individual A and Individual B from the class are randomly paired with each other. Individual A received £10.00 in Northern Ireland and £2.30 in Colombia. Individual A will then have the opportunity to give any amount of his or her money to Individual B. For instance, Individual A may decide to give £0.00 to Individual B and keep £10.00 for him or herself. Or Individual A may decide to give £10.00 to Individual B and keep £0.00 for him or herself. Individual A may also choose to give any other amount between £0.00 and £10.00 to Individual B. This choice will determine how much money each will receive, privately and in cash, at the end of the experiment.” We used a Coordination Game, as described above, to elicit the social appropriateness of each action available to “Individual A,” measuring injunctive norms of pro-sociality before and after the intervention.

##### Measuring injunctive social norms related to smoking

To measure injunctive norms about smoking behavior (i.e., beliefs about the appropriateness of smoking and vaping related actions), we used another Coordination Game. The actions evaluated in this game include: (i) a parent smoking in their own home in front of their children who are under the age of five; (ii) an adult smoking in a car with children under the age of 16 in the car; (iii) someone selling cigarettes to a teenager who looks younger than 16 without requesting proof of age; (iv) a lead actor seen smoking in the opening scene of a recent superhero movie; (v) an older school pupil smoking outside school (e.g., at a bus-stop); (vi) a school pupil using an e-cigarette while walking to school; (vii) a pupil sharing a photo of himself/herself using an e-cigarette on social media (e.g., Facebook, Instagram); (viii) a school pupil using chewing tobacco. We adapted the Krupka and Weber (17) protocol to elicit beliefs about the injunctive norm by asking participants to coordinate with their year group peers in estimating the social appropriateness of various smoking related behaviors on a six point Likert scale that ranges over “extremely socially inappropriate” to “extremely socially appropriate” (i.e., as above their pay-off in the choice task is determined by whether their response matches the most common response given by the year group). By undertaking this Coordination game both pre- and post-intervention, we can identify whether or not some of the target norms (e.g., attitudes related to peer smoking) have changed, while acknowledging that injunctive norms for other behaviors [defining and identifying social norms unrelated to smoking] are not anticipated to be affected by the prevention programs (negative controls). This allows us to create one type of metric with which to understand the effects of the interventions on classroom social norms.

##### Elicitation of expected behavior by others (descriptive norms) related to smoking

To measure a respondent's beliefs about what his/her peers expect of one another regarding smoking and vaping behavior, we adapted the Krupka and Weber protocol (17) to elicit beliefs about expectations that others have for their peers by asking participants to coordinate on a six point Likert scale that ranges from whether: “most of my peers would be accepting of -[behavior]-;““1 = None of my peers; 2 = Only a few of my peers; 3 = Some of my peers; 4 = A lot of my peers; 5 = Most of my peers; 6 = All of my peers.” The personal behaviors being judged here are (i) smoking; and (ii) vaping. *Rationale and Process*: A key condition for a norm to exist is that a respondent believes that others know that there is a norm to perform some behavior and, critically, that others expect them to adhere to the norm. Here we elicit the beliefs of the respondent about that expectation (49). We use this to assess the impact of the intervention on the beliefs about those expectations and therefore on the norms about smoking. Since we are conducting experiments before and after the smoking prevention interventions, we wish to avoid, as far as possible, ascertaining shifts in attitudes that are consequences of merely “learning the right answer” (what the adolescents might believe adults want to hear) as opposed to tapping into the implicit belief norms. This is not a concern in the pre-intervention stage. The actions/behaviors rated in the game are the same actions for which we elicit descriptive norms.

##### Measuring willingness to pay to support anti-smoking norms

Just as a willingness to incur costs to follow the rule in the RF task reveals a respect for norms more generally, a willingness to incur a cost to encourage smoking reduction by others reveals support for anti-smoking norms. Thus, we asked participants to make a donation decision in which they were allocated a sum of money (tokens worth £5.00 in Northern Ireland and £2.30 in Colombia) and they must decide how much of that money they want to keep for themselves and how much they want to donate to the organizations responsible for ASSIST or Dead Cool. Participants were informed that the donations will help ensure that other pupils are more likely to be exposed to these anti-smoking interventions, and thus a donation reveals the participant's belief that such interventions are normatively appealing and effective, providing evidence for a behavioral impact of an injunctive anti-smoking social norm. Participants made the donation decision twice, once *before* the intervention and once *after* the intervention and were told that we would flip a coin to determine which of the two decisions is implemented. Participants' final payments (and donations) depended on the randomly chosen decision. Performing the task twice allowed us to determine if exposure to the intervention increases willingness to donate, and choosing to implement only one of the two decisions ensures that participants have incentives to report their willingness to donate truthfully at both decision times. We would additionally predict a larger effect among those who were more rule-following in the bucket task (i.e., among those who care more about following social norms).

#### Smoking Behavior

At both time-points, pupils had their smoking behavior in the last week measured using a hand-held carbon monoxide monitor (administered by a trained member of the research team). A hand-held PICOAdvantage Smokerlyzer (Bedfont) was used to measure expelled air carbon monoxide from the pupils at the two testing time points. This is an electrochemical sensor which measures carbon monoxide in parts per million (ppm). It measures a range of 0–150 ppm with an accuracy of 2 ppm/5% (whichever is greater).

#### Self-Report Outcomes

Pupils were asked to complete a survey before and after the smoking prevention interventions had taken place to assess their self-reported smoking behaviors and attitudes. Questionnaire items are summarized in Supplementary File 1. All questionnaire items have been validated and adopted from previous studies conducted with children of a similar age. Surveys were delivered via Qualtrics (www.Qualtrics.com) and collected using tablet computers in each school.

##### Socio-demographics

Demographic information was collected in the baseline survey. This included gender, age, home postcode (to capture individual level deprivation based on country specific area level deprivation measures) in Northern Ireland and address to assess socio-economic position from the household, ethnicity and detail on who the pupil lives with (i.e., mother, father, step-parent, sisters/brothers, foster care, other).

##### Smoking behavior (past and present)

At baseline and 1 week after the end of the intervention period, pupils were asked four questions about their current and past smoking behavior. Each question has a unique scaled response appropriate to the question being asked and has been used in previous studies (37, 50).

##### Hypothesized mediators

A range of psychosocial constructs were collected at baseline and 1 week after the end of the ASSIST/Dead Cool interventions. ***Smoking intentions/susceptibility*** were assessed with four questions asking the pupils: (1) if they **do** currently smoke, do they intend to quit smoking in the next 6 months (response on a five-point Likert scale from “Definitely remain a smoker” to “Definitely quit” with an additional response option for “I don't smoke”); (51) (2) do they think they will try a cigarette soon (response “Yes,” “No,” “Don't know”); (37, 52) (3) if one of their best friends were to offer them a cigarette would they smoke it (response on a five-point Likert scale from “Definitely yes” to “Definitely not”); (37, 52) (4) if they **don't** currently smoke, do they intend to take up smoking in the next 6 months (response on a five-point Likert scale from “Definitely remain a non-smoker” to “Definitely start smoking” with an additional response option for “I am a smoker”). (51) ***Self-efficacy*** was assessed using the Lawrance (53) adaptation of the scales outlined in Condiotte and Lichtenstein (54) (with three subscales: Emotional, Friends, Opportunity). ***Perceived risks of tobacco-use*** were assessed using the scales outlined in Halpern-Felsher et al. (55), Song et al. (56), and Aryal et al. (57) (with three subscales: Physical, Social, Addiction). ***Perceived**benefits of tobacco-use*** were assessed using the scales outlined in Halpern-Felsher et al. (55), Song et al. (56), and Aryal et al. (57) (with two subscales: Physical, Social). ***Perceived behavioral control*** was assessed with two questions asking the pupils: (1) how easy they think it would be for them to quit smoking if they smoked regularly (i.e., difficulty to quit); (2) if they decided not to smoke, how sure are they that they could avoid smoking (i.e., avoid smoking) (responses on a five-point Likert scale from “Strongly disagree” to “Strongly agree”) (58). ***Attitudes toward**smoking*** was assessed with the 12-items scale outlined in Ganley and Rosario (59). ***Knowledge of smoking*** was assessed with the six-items scale outlined in Cremers et al. (60). ***Social Norms (injunctive norms)*** and ***Social modeling (descriptive**norms)*** were assessed with the scales outlined in Cremers et al. (60). ***Exposure to**advertising in the media*** was assessed with the 7-items scale outlined in Stigler et al. (61) in Northern Ireland and using a 12-item scale in Colombia, according to the advertising context. An additional item was used to assess ***Exposure to advertising in**shops*** (37).

##### Social networks and pro-sociality

At baseline and 1 week after the end of the intervention period, pupils were asked questions about social networks in their year group (i.e., closest school friends (37), relationship quality, friends who he/she spends most time with outside of school, influential peers) (24). The following final question was added only at follow-up “Can you remember having any conversations with your friends about the risks and benefits of smoking over the past 6 months? If so, how many and with whom?” Pupils were provided with a school year roster in order to help with completion of the social network nominations. Pro-sociality will be assessed with the Need to Belong Scale (62), Fear of Negative Evaluation Scale (63, 64), and Pro-Social Behavior Scale (65).

##### Well-being, absenteeism, other

We assessed the adolescent personality traits (Openness, Extraversion, Agreeableness, Conscientiousness, Emotional Stability) using the *Big Five Trait Short Questionnaire* (BFPTSQ) (66). In Northern Ireland we applied the scaled validation by Morizot (66) and in Colombia we applied the scale validated by Orlet (67). Self-perceived well-being was assessed using the scale developed by the Children's Society, and based on Huebner's life satisfaction scale (37, 68). Rebelliousness and sensation seeking was assessed with the four questionnaire items described in Russo et al. (69); and Dunne et al. (37). Truancy, school education on smoking, and access to and disposal of pocket money was assessed using five questions adapted from Dunne et al. (37).

### Statistical Methods

#### Elicitation of Social Norms and Social Network Analyses

Injunctive social norms will be modeled quantitatively, such that a decision maker's “pay-off” u(a_k_) from a set of actions V {π(a_k_)} is related to the parameter γ ≥ 0, representing the degree to which the individual cares about adhering to social norms, in: u(a_k_) = V {π(a_k_)} + γN(a_k_), with the function N capturing the social norm, [i.e., the social appropriateness of action a_k_ denoted by N(a_k_)]. We let N_g_(a_k_) denote the social norms for group *g*, estimated from the Coordination games. γ is the key parameter reflecting individual sensitivity to the norm, estimated using the total number of balls allocated to the blue “rule following” bucket in the RF task. The Dictator and Coordination games allow us to identify norms related to prosocial behavior and to smoking related activities in the target population. We can then explore whether the norms related to smoking actually do change and whether data from the RF experiments help us predict who is more sensitive to following those changed norms after the intervention. We will also measure correlations (Spearman's rank correlation) between an individual's norms-sensitivity parameter and his/her decisions in the Donation game. We will use tobit regressions that allow for censoring, regressing the distance (Δ_SNdist_) between an individual's choice and the observed average norm (average Dictator choice) in the relevant reference group on his/her norm-sensitivity parameter. The tobit regression allows us to see if there is a statistically significant relationship between norm-sensitivity and the changed norms after the intervention. We will use similar techniques when examining social norms related to tobacco use and individuals' abilities to identify them in the Coordination game. For each behavioral vignette (whose appropriateness is rated), we will calculate a correlation between individuals' norms-sensitivity parameters, and their chosen score on the social appropriateness scale, after calculating (Δ_SNdist_). Scores on the appropriateness scale are categorical, requiring ordered probit regressions. We will conduct the above analysis both pre- and post-intervention but since we will have two observations for each individual, we will use the respective panel random effects versions (including a dummy variable to identify post-intervention observations). In all regressions, we will calculate standard errors clustered on school classes. We will account for individual participants' demographic and psychosocial characteristics, and dummy variables signifying intervention type (ASSIST or Dead Cool intervention) and country (Colombia or Northern Ireland).

${\text{H}}_{0}^{1}$**: that individual psychosocial traits and susceptibility to social norms are independent**: After checking distributional assumptions, multiple linear regression (and where appropriate analysis of variance; ANOVA) will be employed, with any necessary transformations of raw variables; a sample size of 600 in each country achieves 80% power to detect a correlation coefficient of 0.16 for the association between susceptibility to social norms and a continuous psychosocial trait, after adjusting for a design effect of 1.99, assuming a sample of 100 per school and intra-class correlation coefficient (ICC) = 0.01.

${\text{H}}_{0}^{2}$**: that the individual social norms susceptibilities among friendship cliques are uncorrelated**: the analytic approach in this case will be similar to that for ${\text{H}}_{0}^{5}$ which is illustrated in the section sample size for the purpose of power calculation.

${\text{H}}_{0}^{3}$**: that social norms at the class and year group level are independent of social network structure**: a novel aspect of this proposal is that we will examine how social norms sensitivities (Δ_SNdist_) cluster among friendship groups (before and after the two interventions), and thus examine possible mediating mechanisms for the intervention effects and whether they are moderated by social network structure. We will extend the clustering method presented by Grimmer and King (70), using a Markov Chain Monte Carlo (MCMC) model to integrate various attributes of the students and their social norms sensitivity parameters in the first step of the *a posteriori* clustering selection framework. Examining the influence of individual student attributes (their norms sensitivities; psychosocial traits like self-efficacy, and the number of family members who smoke) within a MCMC framework permits inference based on well-known expectation and maximization algorithms. We note that peer influence was inferred using hidden Markov models (7) applied to *before* and *after* data from three ASSIST schools, but with a similar per country sample size as Steglich et al. (7), we will obtain superior experimental measures of norms and thus populate the MCMC models with real rather than inferred parameters. If homophily is not stable over one semester, in a sensitivity analysis we will use an instrumental variable approach, instrumenting on orthogonal characteristics of students not nominated by the ego but who were friends of their friends, using characteristics that should not plausibly predict the egos' norms sensitivity (Δ_SNdist_), nor friendship structure (71).

${\text{H}}_{0}^{4}$**: that the changes in smoking related norms are the same in schools which were offered the ASSIST intervention and in those which were offered the Dead Cool intervention**: we will use a regression based approach permitting adjustment for the multilevel clustered nature of the data, comparing the change in smoking related norms (identified through the Coordination games) in ASSIST and Dead Cool Schools and between UK and Colombian Schools.

${\text{H}}_{0}^{5}$**: that any changes in social norms are independent among members of the same friendship clique**: see section sample size.

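### The smoking-norm regressions on rule-following measure how well pupils identify the group norm, not whether they follow it, and the analysis given for H0-4 leaves out the own-conduct question the protocol poses

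*Protocol article*

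**What the plan says.** All references are to the protocol article.

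- **The parameter.** Elicitation of Social Norms and Social Network Analyses sets a pupil's utility from an action as a payoff term plus gamma times the norm. Gamma is described as "representing the degree to which the individual cares about adhering to social norms", and it is "estimated using the total number of balls allocated to the blue" bucket in the Rule-Following (RF) task.
- **The question.** The same section wants to learn "whether data from the RF experiments help us predict who is more sensitive to following those changed norms after the intervention".
- **The regressions.** A tobit model regresses distance from the group's average norm on gamma, with this reading: "The tobit regression allows us to see if there is a statistically significant relationship between norm-sensitivity and the changed norms after the intervention". Similar techniques are then applied to tobacco norms and "individuals' abilities to identify them in the Coordination game". For each vignette, gamma is related to "their chosen score on the social appropriateness scale", using ordered probit.
- **The incentive.** Under Measuring injunctive and descriptive norms, pupils are rewarded for matching other pupils' answers "rather than to provide their personal opinions". Measuring injunctive social norms related to smoking applies the same rule to the smoking items.
- **H0-4.** In the research questions it concerns changes in smoking attitudes, intentions and behaviors in relation to individual norm sensitivity and group norms. In the Statistical Methods it becomes a comparison of change in Coordination-game norms between interventions and between countries.

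**The concern.** Gamma is a weight used when a pupil chooses what to do. Whether it predicts who follows a changed smoking norm is a question about conduct. The outcome in the smoking regressions is an incentivised guess at what others will say. A pupil who does not care about norms at all has the same financial reason to guess well as one who cares a great deal.

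A null result could then be reported as evidence that norm-sensitive pupils did not take up the new norm, when the test could not have shown it. A positive result could be reported as norm-following when it shows only that attentive or perceptive pupils do better in both tasks. For a study about mechanisms, this affects a central inference.

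**Working it through.** **1. The plan's own power figures.** No power is stated for the gamma-versus-rating regressions. Two other tests have figures, and both reproduce (two-sided 5% assumed):
- H0-5: n = 300 and slope 0.16 give power of 0.794 (Fisher z), 0.799 (noncentral t) or 0.802 (Wald), against a stated value of over 80%.
- H0-1: design effect 1 + 99 × 0.01 = 1.99; effective n 600 / 1.99 = 301.5; power 0.796 to 0.804.

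Neither figure applies to the regressions discussed here.

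**2. Where gamma enters.**
- Choosing conduct a: u(a) = V{π(a)} + gamma × N(a). Gamma matters.
- Choosing a rating r in the Coordination game: expected pay = prize × Pr(most common answer = r). Gamma does not appear, so the best rating is the same for gamma = 0 and for a large gamma.

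The game is therefore well suited to estimating N_g and poorly suited as an outcome for gamma.

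**3. Other places where conduct might be tested.**
- *Dictator part.* The section on norms unrelated to smoking describes a hypothetical vignette rated in a Coordination game. No own Dictator choice is described, so the tobit on distance from the average Dictator choice has no described conduct data.
- *H0-3.* The rating distance is itself labelled as norm sensitivity there, which carries the same confusion forward.
- *Donation game.* This is a costly own choice, correlated with gamma by Spearman's rank correlation. It concerns support for prevention programs, and the group norm is not in the analysis.
- *Mediation analyses.* These are repeated for smoking behavior and intentions, but gamma is not named in them.

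**4. Illustrative simulation.** Every setting is an assumption: 1,200 pupils, 2,000 runs, six-point ratings, no clustering, and a Spearman test in place of tobit or ordered probit. Gamma is standard normal. The group norm is 2.0, guesses have error SD 0.9, and own preference has mean 3.5 and SD 1.2. Conduct is a weighted average of norm and preference, with weight on the norm 1 / (1 + exp(−s × gamma)).

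| s (strength of norm-following) | gamma v rating distance: share significant | gamma v distance of conduct from norm: share significant |
|---|---|---|
| 0 | 0.047 | 0.051 |
| 0.15 | 0.043 | 0.935 |
| 0.5 | 0.052 | 1.000 |
| 1.0 | 0.053 | 1.000 |

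With s = 0.5 and 30% of pupils giving their own view instead of a guess, the rating test rejects in 0.057 of runs.

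Next, set s = 0 (no norm-following) and let the guess-error SD be 0.9 × exp(−c × gamma). For c = 0.05, 0.10 and 0.20, exp(−c) = 0.951, 0.905 and 0.819, so error falls by about 5%, 10% and 18% per SD of gamma. The rating test then rejects in 0.339, 0.867 and 1.000 of runs.

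**5. A second illustration: careless answering.** Let a share p of pupils answer both tasks at random. Assume balls with mean 35 (SD 12) for attentive and 25 (SD 10) for careless pupils, and distance with mean 0.8 (SD 0.6) and 1.7 (SD 1.0).
- cov = p(1−p) × 10 × (−0.9)
- var(balls) = 144(1−p) + 100p + 100p(1−p)
- var(distance) = 0.36(1−p) + p + 0.81p(1−p)

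At p = 0.10: −0.81 / √(148.6 × 0.4969) = −0.094. At p = 0.20: −1.44 / √(151.2 × 0.6176) = −0.149. A correlation in the direction expected of norm-following appears without any.

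**The case against.** The defence has four parts.

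- **The text does not plainly equate ratings with following.** The aim is worded as something to explore. The Donation-game correlation comes next, and the smoking ratings appear later under a label that is already norm identification. This is fair. However, the sentence interpreting the tobit does link gamma to the changed norms, the smoking ratings inherit that approach, and no other smoking model is given for the aim.
- **Gamma is tested on an own choice.** The Donation game is incentivised and made before and after the intervention, and a larger effect is predicted among rule-followers. A reader might infer that the study never relates gamma to conduct, and that would be wrong. What stands is that donating to a program is not following a changed smoking norm, and that the planned correlation has no norm term.
- **The own-conduct question is already posed, and its model may sit in a fuller plan.** H0-4 in the research questions does pose it. But the article is not silent on the analysis: it gives one, with a restated null from which gamma and behavior are gone. The two statements of H0-4 differ within the document.
- **The gamma slope need not be zero.** Gamma could relate to ratings through attention, accuracy or treating the instruction to match as a rule. This is correct. A reader might infer that the slope must be zero and power 5% at any sample size, but that holds only if guessing error is unrelated to gamma. The concession does not rescue the test, because none of these routes is norm-following.

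It also stands that this is a proof-of-concept study and that the remedy has limited precision.

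**Conclusion.** The concern holds for the smoking-norm regressions on Coordination-game ratings, not for the study as a whole. Those regressions can show who identifies the norm. They cannot show who follows it, in either direction. That conclusion rests on the payment rule and the definition of gamma in the article and does not depend on the simulated figures.

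The size is conditional. If guessing error is unrelated to gamma, the test rejects at about 5% whatever the strength of norm-following. If gamma reduces guessing error by roughly 5% to 18% per SD, it rejects in 34% to 100% of runs with no norm-following. These rates come from assumed settings without clustering, and the near-certain power for conduct in the same runs is a contrast, not a forecast for this study. The careless-answering correlations are likewise illustrations. It would be wrong to set them against the 0.16 in the power statements, which belongs to a friend-network slope and a trait correlation.

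The accompanying defect is firmer: H0-4 as posed and H0-4 as analysed are different hypotheses. The plan should be changed, at moderate priority.

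**What to change.** 1. Keep the Coordination games to estimate N_g and its change.
2. Relabel the regressions of rating, or rating distance, on gamma as analyses of norm identification, and state that they will not be read as norm-following. Amend the sentence interpreting the tobit and the H0-3 label accordingly.
3. Restore H0-4 as posed in the research questions. Model follow-up intention or susceptibility, and smoking behavior, on baseline value, baseline gamma, intervention and country, with school-level inference.
4. Add change in the year-group norm and its interaction with gamma as exploratory terms, reported with confidence intervals.
5. Keep the comparison of norm change between interventions and countries as a separately named analysis.

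**Cost.** No new data are needed: gamma, intentions, self-reported smoking and carbon monoxide are all collected. The work is one added family of regressions and some relabelling. The limits should be stated openly. There is one year group in each of 6 + 6 = 12 schools, so norm change takes only 12 values and the interaction will be imprecise. The intention outcomes are self-reported, and the article itself warns that pupils may learn the expected answer after the intervention.
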